### **Statistical Methods**

The analysis of the trial feasibility aims will be primarily descriptive. Summary statistics will be calculated to assess aims such as the recruitment and retention rate, frequency of access and use over time of the E-health platform. A list of key study variables will be drawn up and the proportion missing by time point and arm will be calculated.

All intervention effectiveness outcome measures will be summarised by intervention arm using means and standard deviations or median (range, IQR) for continuous outcomes (as appropriate), and frequencies and proportions for categorical outcomes. As this is a feasibility study with only 30 participants per arm the trial will be underpowered to detect statistically significant differences in outcome measures between arms, however the difference between arms will be estimated and presented with 95% confidence intervals to indicate the uncertainty of the estimate. The estimation analyses will be undertaken using an intention-to-treat approach i.e. participants will be analysed in the arm to which they were randomised regardless of whether or not they subsequently used self-help online or via usual care approach or their adherence to the intervention.

The time to a two point increase in CAT score will be plotted using the method of Kaplan-Meier and Cox proportional hazards model will be used to estimate the relative 'risk' between arms by means of a hazard ratio. An analysis of covariance model will be used to obtain an estimate for the mean difference in CAT score at final study visit (90 days) between the two intervention arms adjusted for baseline CAT score. In addition CAT values over time will be plotted for individual and the mean value over time displayed by intervention arm. A longitudinal analysis will then be undertaken using a linear mixed model including baseline CAT as a covariate with random subject effects using (if possible) a structured (symmetrical) covariance matrix. Model assumptions will be assessed through residual analysis.

Every effort will be made to obtain 90- day follow up data for all participants including those that have withdrawn from the trial by offering a home visit if required to obtain this information.

The mean difference in the number of critical errors between arms will be estimated by fitting a Poisson regression model. If there is over dispersion due to a high number of zero errors then a zero-inflated Poisson regression model will be used or an over dispersion parameter will be included into the model.

The mean difference in St Georges Respiratory Questionnaire, Modified MRC dyspnoea, PAMs and Hospital Anxiety and Depression between arms at the

final study visit will be estimated using analysis of covariance model including the baseline value of the score as well intervention arm as a covariate in the model. Time to exacerbation will be analysed in a similar manner to the two point increase in CAT score.

The number of adverse events (AE) and serious adverse events (SAE) will be tabulated by arm for each event and also by the number of patients reporting an event. No dictionary for coding adverse events will be used. Events will be recoded using terms of the clinical investigators choosing.

A full statistical analysis plan will be drawn up and agreed by the PI and study team prior to the final data extraction.

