### **Purpose of trial**

In a group of patients with COPD, discharged from hospital with an acute exacerbation at their 2 week review we will undertake a feasibility trial to test the design and obtain preliminary evidence that the MyCOPD web based self-management plan will result in greater improvements in quality of life scores, faster recovery to baseline, and fewer errors in inhaler technique compared to conventional paper based plans. The result from this trial will inform the design and sample size calculation for a definitive trial to determine the effectiveness MyCOPD

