**Intervention effectiveness outcomes**

- The time to a two-point improvement in the COPD Assessment Tool (CAT) Score
- The improvement in CAT score at study completion 90(+/- 7) days in the MyCOPD support population compared to usual care
- The number of critical errors by inhaler at study completion 90(+/- 7)
- St Georges Respiratory Questionnaire (SGRQ) score at study completion 90(+/- 7)
- Modified MRC dyspnoea score at study completion 90(+/- 7)
- Patient Activation Measure (PAMs) score at study completion 90(+/- 7)
- Hospital Anxiety and Depression Score (HADS) at study completion 90(+/- 7)
- WPAI score at study completion 90 (+/- 7)
- VSAQ score at study completion 90 (+/- 7)
- COPD treatment adherence (what would be monitored and how would this be measured?)
- The number of exacerbations by study completion 90(+/- 7) days
- The time to exacerbations
- The rate of and timing of antibiotic use by study completion 90(+/- 7) days
- The rate of and timing of steroid use by study completion 90(+/- 7) days
- Safety the number of AEs and SAEs by study completion 90(+/- 7) days

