### **COPD Assessment Tool (CAT) Questionnaire**

This is a validated symptom scoring system used in COPD studies The CAT questionnaire contains eight questions and provides a reliable measure of the impact of COPD on health status. Patients read the two statements for each item, which describe the best and worst scenario, (e.g I never cough – I cough all the time), and decide where on the scale of 0-5 they fit. The maximum score is out of 40. The higher the CAT score the greater the impact of symptoms on their health status. Experts involved in the development of CAT suggest that any change of 2 or more in the patient's final score may indicate a clinically significant change.

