#### **Sample size rationale**

In this trial the main aim is to assess the feasibility of undertaking a fully powered trial in this area. As a result the sample size has been chosen with consideration to estimating a number of parameters with sufficient precision and not based on the number required to test a hypothesis.

If we approach one hundred and twenty participants to take part in this trial and assume a recruitment rate of 50% this would enable us to estimate the 95% confidence intervals for the recruitment rate with precision of at least  $\pm 9$  percentage points. With 60 participants recruited to the trial (  $n=30$  per arm), we would be able to estimate the 95% confidence intervals for the withdrawal/dropout rate with precision of at least  $\pm 7$  percentage points if the true withdrawal/dropout rate was 9%.

We also would like to obtain a sample size sufficient to obtain a good estimate for the variance of each of the potential primary outcomes. The variance estimate of the chosen primary outcome would then be used to inform the power calculation for a definitive trial. Guidelines for sample size to estimate

the variance vary, but typically range between 24-50 participants as a result we think that 30 participants per group will be sufficient.

We will also estimate the difference between arms with 95% confidence intervals. In our pilot work we observed that CAT had a standard deviation of 6.5, if this observation is found to hold in this study we would be able to estimate the difference in CAT between arms with 95% confidence interval width of  $\pm 3.3$ .

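### The CAT time-to-event analysis is written for a two-point rise, which is a worsening, while the listed outcome is a two-point improvement

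*Protocol*

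**What the plan says.** The protocol's list of intervention effectiveness outcomes opens with "The time to a two-point improvement in the COPD Assessment Tool (CAT) Score". The section describing the CAT questionnaire sets out eight items scored 0 to 5 and says "The higher the CAT score the greater the impact of symptoms on their health status". It also gives the range, "The maximum score is out of 40", and the source of the threshold: "any change of 2 or more in the patient's final score may indicate a clinically significant change".

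Statistical Methods then gives the analysis: "The time to a two point increase in CAT score will be plotted using the method of Kaplan-Meier and Cox proportional hazards model" is to be used to obtain a hazard ratio between arms. Later the same section refers back to that event: "Time to exacerbation will be analysed in a similar manner to the two point increase in CAT score".

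The Purpose of trial section says what the comparison is meant to show for myCOPD. Besides better quality-of-life scores, it names "faster recovery to baseline, and fewer errors in inhaler technique compared to conventional paper based plans".

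**The concern.** On a scale where higher is worse, a two-point increase is a deterioration. The outcome list and the analysis text therefore name events in opposite directions. An analyst who codes the event from Statistical Methods would count patients who get worse and would censor those who only recover.

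Three things are at stake:

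- The listed outcome, time to improvement, would have no analysis, and the analysed event, time to worsening, is not on the outcome list.
- The hazard ratio changes meaning. Above 1 is good for myCOPD if the event is improvement and bad if it is worsening. A reader who goes by the outcome list would draw the reverse conclusion.
- The trial is meant to inform the choice of primary outcome and the sample size of a definitive trial. An event frequency taken from this analysis would belong to a different event. This is also the only time-to-event analysis of recovery in the plan.

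**Working it through.** **1. The direction of each statement**

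| Protocol section | Event or direction | Meaning on the CAT scale |
|---|---|---|
| Intervention effectiveness outcomes | two-point improvement | fall of 2 or more |
| COPD Assessment Tool (CAT) Questionnaire | higher score, greater symptom impact | a rise is a worsening |
| Purpose of trial | faster recovery | fall |
| Statistical Methods, Kaplan-Meier and Cox | two-point increase | rise of 2 or more |
| Statistical Methods, time to exacerbation | refers back to the two-point increase | rise of 2 or more |

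No section reverses the score or defines an increase as a gain. The two-point threshold is stated for change in either direction, so it does not settle the question. The contradiction follows from these statements without any calculation.

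**2. The plan's own CAT figure**

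The Sample size rationale states a 95% confidence interval of ±3.3 for the difference in CAT between arms: "In our pilot work we observed that CAT had a standard deviation of 6.5", with 30 per arm.

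Half-width = 1.96 × 6.5 × √(2/30) = 1.96 × 6.5 × 0.2582 = 3.29.

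The figure reproduces. It concerns a difference in means and does not depend on the direction of the event. The protocol gives no event rate or hazard ratio for the time-to-event analysis, so there is no planned figure to check there.

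**3. Illustration of the consequence**

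The inputs are assumptions, not protocol figures:

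- CAT change from Visit 1 at days 30, 60 and 90, with the mean moving linearly to the day-90 value shown.
- Between-patient SD of change 3, within-patient SD 3 or 5, changes rounded to whole points.
- 10,000 simulated patients per arm. The event is the first visit at which the threshold is met. Cox model with Efron handling of ties.

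| Mean day-90 change, written plan / myCOPD | Within-patient SD | Ever fall ≥2, written / myCOPD | HR for fall | Ever rise ≥2, written / myCOPD | HR for rise |
|---|---|---|---|---|---|
| −2 / −4 | 3 | 74% / 85% | 1.31 | 46% / 36% | 0.73 |
| −2 / −4 | 5 | 80% / 88% | 1.22 | 61% / 52% | 0.79 |
| −3 / −5 | 3 | 80% / 90% | 1.31 | 41% / 30% | 0.71 |
| −3 / −5 | 5 | 84% / 90% | 1.22 | 56% / 45% | 0.77 |
| −1 / −4 | 3 | 67% / 85% | 1.57 | 54% / 35% | 0.58 |
| −1 / −4 | 5 | 76% / 87% | 1.35 | 66% / 50% | 0.68 |

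With 30 per arm and no withdrawals, the expected number of patients with the event is 30 × (sum of the two proportions). For a fall this runs from 30 × (0.67 + 0.85) = 45.6 to 30 × (0.84 + 0.90) = 52.2. For a rise it runs from 30 × (0.41 + 0.30) = 21.3 to 30 × (0.66 + 0.50) = 34.8.

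The same benefit therefore appears on opposite sides of 1. Many patients have both events at different visits, so time to worsening is a different quantity and not simply the inverse of time to improvement.

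**4. How far the illustration can move**

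At a single mean fall of 3 points, the SD of change was varied from 3 to 6.5, the fall was made linear or immediate, and persistent patient-level variation was allowed. The proportion ever falling by 2 or more then ranged from 71% to 89%, and the proportion ever rising from 13% to 53%. With no true mean change and an SD of change of 4, both are 60%. The gap in frequency depends on how much patients recover; the change in meaning of the hazard ratio does not.

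**The case against.** The strongest reply is that this is a drafting slip in a trial where it can do little harm. The protocol names no primary outcome, declares the comparison between arms underpowered, and bases its sample size on recruitment, dropout and variance. The analysis of covariance at 90 days, the mixed model and the plots of CAT over time are unaffected, and they also bear on recovery. The outcome list and the stated purpose both point to improvement. The quotation marks that the protocol puts around the word risk suggest that the authors had a favourable event in mind. The sentence on time to exacerbation only carries the phrase forward, so it is not independent confirmation. A full statistical analysis plan is also promised and may already have put this right.

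Most of this is fair, and it limits the consequence. It does not remove the contradiction. A two-point worsening is also a meaningful event under the protocol's own threshold, and the text pairs it with time to exacerbation, which is unfavourable, so an analyst could follow the wording in good faith. Nor is this a detail normally left for later: the protocol does state the event, in two opposite directions. The trial is not blinded, and the analysis plan need only be agreed before the final data extraction, so the direction should not remain open while CAT scores accumulate. Whether an analysis plan corrects the wording cannot be judged from the protocol.

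**Conclusion.** The concern holds. As worded, Statistical Methods defines the opposite event from the listed outcome, and the protocol's own description of the CAT settles which direction is which. That conclusion needs no assumption.

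The numerical size is illustrative only. Under the assumed changes, 67–90% of patients per arm would have a fall of at least 2 points against 30–66% with a rise, and a benefit of myCOPD would show as a hazard ratio of 1.22–1.57 or 0.58–0.79 depending on which event is coded. The ±3.3 precision and the other CAT analyses stand. Because the error reverses the meaning of a listed outcome and costs almost nothing to correct, it should be corrected before any analysis.

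**What to change.** In Statistical Methods, replace the two-point increase with a two-point improvement, defined as the first CAT score at least 2 points below the Visit 1 score. Make the same change in the sentence on time to exacerbation, and match the wording to the outcome list.

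State the direction of benefit for each hazard ratio separately. After the correction, a value above 1 favours myCOPD for CAT improvement, while a value below 1 favours it for time to exacerbation, so a cross-reference between the two analyses is no longer enough.

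Say that the event is taken from the CAT recorded at the scheduled day 30, 60 and 90 contacts in both arms. The app screenshots in the supplementary material note that users also complete a CAT on first access and every four weeks, so without this rule the myCOPD arm could have extra occasions on which to record the event.

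If time to worsening is also of interest, list it as a separate outcome.

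The cost is a wording change in the protocol, carried into the statistical analysis plan if it uses the same text. Data collection and sample size do not change.

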### **Background and Significance**

COPD is characterised by airflow obstruction that is not fully reversible. The airflow obstruction is usually progressive in the long term and results in the gradual development of limiting symptoms such as cough and breathlessness. Cigarette smoking is the predominant cause of COPD, but other factors, particularly occupational exposures, may also contribute to the development of COPD. Exacerbations occur when there is a rapid and sustained worsening of symptoms beyond normal day-to-day variations, these are often associated with acute respiratory infections and can result in unscheduled health care use and hospitalisation.

There are currently 900,000 patients diagnosed with COPD in the UK. COPD is the second leading cause for hospital admission in the UK; recent figures show that one in three people with COPD is readmitted within 28 days of discharge. The latest Quality Standards for COPD from the National Institute for Health and Care Excellence (NICE) highlights the importance of self-management for patients and recommends that every person diagnosed with COPD be given an individualised comprehensive self-management plan. Self-management has been shown to be associated with health service utilisation by COPD patients, improve their quality of life and reduce hospitalisation.

Patients with COPD are often prescribed a complex combination of inhaled medications in a variety of devices; these medications differ enormously in their delivery method and periodicity. This complexity contributes to poor compliance and therefore wasteful prescribing and it is estimated that there is currently only at best a 30% compliance to COPD medications.

The majority of COPD action plans are delivered in a written (paper) format, and currently a validated online interactive solution does not exist. *MyCOPD* has been designed and programmed by my mhealth Ltd with patient and clinician involvement. It is a web-based self-management system designed to encompass the principles of supporting self-care in people with COPD. The system can be easily and securely accessed online by patients and healthcare

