### **Visit 1- Consent and Screening**

Patients wishing to participate as above, will within 2 weeks of hospital discharge (+/- 1 week) at Visit 1 initially give written informed consent. This visit may occur at the hospital, in primary care or at the patient's home depending on patient preference.

Clinical data will be captured. Symptom scores will be calculated using the COPD Assessment Tool (CAT), SGRQ, modified Medical Research Council Dyspnoea Questionnaire (mMRC) Patient Activation Measure (PAM), Work Productivity Activity Impairment (WPAI) and the Veterans Specific Activity Questionnaire (VSAQ). At this visit the team will also record the admission and exacerbation history, video the inhaler technique and complete an inhaler critical errors assessment.

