### **Inhaler Technique**

As different inhaled medication devices require different techniques, each participant's inhaler technique will be assessed according to manufactures guidelines for each device and critical errors recorded. Their technique will be video recorded at visit one and visit two. Any changes to devices during the study will be recorded prior to starting any new treatment. Each participant's technique will be evaluated as either GOOD or POOR and the number of critical errors recorded. Each device will have its own critical error list we have created based on manufactures guidelines.(Appendix 4)

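### The Poisson model for inhaler critical errors names no baseline covariate, although the same count is taken before randomisation and the other modelled scores are adjusted for theirs

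*Protocol*

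**What the plan says.** All of this is in the protocol.

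- Statistical Methods, critical errors: "The mean difference in the number of critical errors between arms will be estimated by fitting a Poisson regression model". If excess zeros cause over-dispersion, "a zero-inflated Poisson regression model will be used or an over dispersion parameter will be included into the model". Neither sentence names a covariate.
- Statistical Methods, other scores: the 90-day CAT difference is estimated "between the two intervention arms adjusted for baseline CAT score", and the longitudinal CAT model also carries baseline CAT. SGRQ, mMRC, PAM and HADS are "estimated using analysis of covariance model including the baseline value of the score as well intervention arm as a covariate".
- Visit 1: the team will "video the inhaler technique and complete an inhaler critical errors assessment". The Randomisation text in the Statistical Section places allocation after all baseline data are collected. Appendix 1 shows the critical-error sheet at Visit 1 and at the end of study.
- Inhaler Technique: "each participant's inhaler technique will be assessed according to manufactures guidelines for each device and critical errors recorded".
- The synopsis lists the outcome as an improvement in the number of critical errors. The body lists it as the number by inhaler at study completion.
- Randomisation is 1:1 in permuted blocks, with no stratification factor named.

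**The concern.** Among the measures taken at both Visit 1 and day 90 for which the section names a model of the final value, critical errors are the only one without a baseline term. An outcome framed in the synopsis as an improvement points to a baseline value, and that value is already on file for each participant.

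Critical errors have their own analysis line in the synopsis, and a stated objective is to find the most suitable primary outcome for the definitive trial. If this candidate is summarised without baseline adjustment while its rivals are summarised with it, it can look noisier than it needs to. With 30 per arm and no stratification, chance differences in starting technique also stay in the arm estimate. The interval allows for them, but at the cost of width.

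**Working it through.** **The plan's own precision figure.** The protocol gives no figure for critical errors. Its only between-arm figure is for CAT: 1.96 × 6.5 × √(2/30) = 3.29, which matches the stated ±3.3. So 30 per arm is the right base for what follows.

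**Effect of a baseline covariate, by formula.** If ρ is the correlation between Visit 1 and day-90 values, adjustment multiplies the variance of the arm estimate by 1 − ρ² and the interval width by √(1 − ρ²). The equivalent unadjusted size is 30/(1 − ρ²) per arm. The values of ρ are assumed.

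| ρ | Width factor | Narrower by | Equivalent n per arm |
|---|---|---|---|
| 0.3 | √0.91 = 0.954 | 5% | 30/0.91 = 33 |
| 0.5 | √0.75 = 0.866 | 13% | 30/0.75 = 40 |
| 0.7 | √0.51 = 0.714 | 29% | 30/0.51 = 59 |

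**Check on counts.** The formula belongs to linear models, so it was checked by simulating Poisson regression with an estimated dispersion, 30 per arm, 1,500 runs per row. All inputs are assumptions: a true rate ratio of 0.7, a baseline mean of 1 to 2 errors per device, a 20% fall in the control arm, and a patient-level SD of 0.3 to 0.8 on the log scale. Either every patient has one device, or 1, 2 and 3 devices occur in 40%, 40% and 20%. The covariate is log(baseline count + 0.5). The last column uses the baseline rate per device with log(devices) as offset, the number of devices being the same at both visits.

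| Mean per device, SD, devices | Count correlation | SD of log ratio, arm only | With baseline count | Ratio | √(1−ρ²) | Ratio with devices too |
|---|---|---|---|---|---|---|
| 1, 0.3, one | 0.07 | 0.358 | 0.358 | 1.00 | 1.00 | 1.00 |
| 1, 0.6, one | 0.25 | 0.376 | 0.366 | 0.97 | 0.97 | 0.97 |
| 1, 0.3, 1–3 | 0.28 | 0.279 | 0.270 | 0.97 | 0.96 | 0.92 |
| 1.5, 0.6, one | 0.33 | 0.317 | 0.304 | 0.96 | 0.94 | 0.96 |
| 1, 0.6, 1–3 | 0.47 | 0.329 | 0.293 | 0.89 | 0.88 | 0.87 |
| 2, 0.8, one | 0.55 | 0.347 | 0.283 | 0.82 | 0.84 | 0.82 |
| 1.5, 0.6, 1–3 | 0.56 | 0.296 | 0.243 | 0.82 | 0.83 | 0.81 |
| 2, 0.8, 1–3 | 0.73 | 0.343 | 0.227 | 0.66 | 0.68 | 0.67 |

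Three things follow.

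1. The formula is a fair guide for these counts.
2. The mean estimated ratio was 0.68 to 0.70 with and without the covariate, so what changes is precision and not the target.
3. Device number adds at most about 5 points beyond the baseline count (0.97 to 0.92) and almost nothing at high correlation.

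In these runs the mean baseline count differed between arms by 25% or more in 37% to 49% of trials.

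**The case against.** **The SAP may supply the term.** The section promises a full SAP before final data extraction, and it never says that this analysis is unadjusted. The Cox models name no covariates either, and a baseline term is part of what analysis of covariance means. A reader might infer that the protocol commits to an arm-only model. It does not; it is silent. What remains is that the section settles the baseline covariate for five scores and omits it for this one, so a SAP that followed the text literally would leave it out.

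**Bias.** A reader might infer that chance imbalance makes the estimate wrong. Under 1:1 randomisation it does not, and a correctly computed interval already allows for imbalance. The trial is estimation-only and names no primary outcome, and the stored data would allow an adjusted variance to be computed later for the definitive trial.

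**Devices.** The background notes that "Patients with COPD are often prescribed a complex combination of inhaled medications in a variety of devices", and the Appendix 4 lists run from 6 steps (Easyhaler, Easibreathe) to 10 (Breezehaler). It is tempting to conclude that an exposure offset has been wrongly left out. The documents do not go that far. Device number is not a named Visit 1 variable and can only be derived from the per-device sheets. The outcome is listed by inhaler, so a patient total may not be what is analysed. The protocol also expects devices to change during the study, so a day-90 device or step count is post-randomisation.

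**Mean difference.** Calling a Poisson result a mean difference might look like an error. No link is stated, and a mean difference can be obtained from the fit, so this is only a matter of wording.

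**Size of gain.** Training may weaken the link between the two visits, since myCOPD includes technique videos. With step errors assumed to fall from 18% to 7% and a within-patient skill correlation of 0.5, the gain from both terms was 6–7% with 1–3 devices and 1% with one. This objection stands, and it is why no single figure can be claimed.

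**Conclusion.** The point holds as a limited one. The critical-error model omits a baseline covariate that is collected before randomisation and that the section uses for every comparable score. The likely consequence is an unbiased but wider interval than necessary, and a less even basis for comparing candidate primary outcomes.

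Over the assumed range the gain in precision runs from nil to about a third. It is about 5%, 13% and 29% of interval width at a correlation of 0.3, 0.5 and 0.7. Because the documents give no mean, variance or correlation for errors, the upper end should not be taken as the expected value. No test or safety decision depends on this. The change is worth making because it costs almost nothing.

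**What to change.** In the critical-error paragraph of Statistical Methods, state that the day-90 count will be modelled on arm and the Visit 1 critical-error count, for example log(count + 0.5), and that the same covariate enters the over-dispersed or zero-inflated variant. Report the rate ratio with its 95% confidence interval, and the mean difference obtained by standardising the fitted model over the trial's participants.

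State whether the analysed count is per inhaler or a patient total. If it is a total over several inhalers, the number of devices or checklist steps assessed at Visit 1 may be added as a covariate. The day-90 number should not be used, because it arises after randomisation.

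The cost is one or two sentences in the protocol or SAP. No new data, visits or participants are needed.

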### **Exacerbation History**

The numbers of COPD exacerbations requiring oral antibiotics and/or oral steroids by the participants one year prior to starting the study will be recorded at visit one. If the participant has any exacerbations requiring oral antibiotics and/or steroids required during the period of the study this will be recorded at visit two.

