### **Statistical Section** 

#### **Randomisation**

Patients will be randomised to MyCOPD E-health platform or written self-support platform at the end of visit 1. Randomisation will take place using permuted blocks in a ratio of 1:1 to either platform MyCOPD or written plan (Standard of Care).

Once a patient is consented, all baseline data collected and eligibility confirmed, a study staff will randomise participants to the study using an online randomisation system developed and hosted by my mhealth Ltd.

As this is a web based tool the study staff member will log in to the website using their unique user code and password. They will then enter the participants screening number, initials and the date of the visit. This will then generate a unique randomisation number and inform the user, which study arm the participant will receive either written SMP or online SMP.

Emergency code break will not be required in this study, due to the nature of the intervention.

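### The Cox model for time to exacerbation names no covariate, although each patient's prior-year exacerbation count is recorded before an unstratified randomisation

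*Protocol*

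**What the plan says.** Under Statistical Methods, the Protocol handles this outcome by cross-reference: "Time to exacerbation will be analysed in a similar manner to the two point increase in CAT score". The method referred to is a Kaplan-Meier plot plus a model described as follows: "Cox proportional hazards model will be used to estimate the relative 'risk' between arms by means of a hazard ratio". No covariate is named in either place.

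Elsewhere in the same section the baseline covariate is named. The CAT analysis of covariance compares scores "between the two intervention arms adjusted for baseline CAT score". The CAT mixed model includes baseline CAT. The four questionnaire analyses are specified as "including the baseline value of the score as well intervention arm as a covariate in the model".

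The section on Exacerbation History says that the number of "exacerbations requiring oral antibiotics and/or oral steroids by the participants one year prior to starting the study will be recorded at visit one", and Appendix 1 ticks this item at Visit 1. Randomisation comes at the end of that visit, once baseline data are complete, and is described thus: "Randomisation will take place using permuted blocks in a ratio of 1:1 to either platform MyCOPD or written plan (Standard of Care". No stratification factor is given.

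**The concern.** Patients with COPD can differ widely in how often they exacerbate, and the count in the year before entry is the baseline version of this outcome. As written, neither the allocation nor the named model uses it. Two consequences follow.

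- **Chance imbalance.** With 30 per arm and no stratification, one arm can by chance hold more of the frequent exacerbators. A model without the count attributes the resulting difference in hazard to the intervention.
- **Attenuation.** When individual hazards vary and the true ratio is not 1, a Cox model without the prognostic variable gives a ratio closer to 1 than the ratio for an individual patient.

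These comparisons are for estimation. The Purpose of trial section wants preliminary evidence of effect and input to the definitive trial's design, and the Objectives include choosing that trial's primary outcome. A hazard ratio that partly reflects baseline risk serves those aims less well.

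**Working it through.** **1. The plan's own figures.** The Sample size rationale gives three half-widths, and all reproduce:

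- Recruitment: 1.96 × √(0.5 × 0.5 / 120) = 0.089 (stated 9 points).
- Dropout: 1.96 × √(0.09 × 0.91 / 60) = 0.072 (stated 7 points).
- CAT difference: 1.96 × 6.5 × √(2/30) = 3.29 (stated 3.3).

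None concerns time to exacerbation, for which no rate, spread or target hazard ratio is given.

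**2. How often the arms differ by 0.5 SD.** The SD of a standardised arm difference at 30 per arm is √(2/30) = 0.258. A difference of 0.5 is 0.5 / 0.258 = 1.94 such units, which has a two-sided probability of about 5%. Simulation gave 4.7% to 5.8%.

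**3. Simulation inputs.** From the Protocol: 60 patients, 1:1 allocation, 90 days of follow-up. Assumed: gamma-distributed individual rates with mean 2 or 3 per year and shape 0.7, 1 or 2 (a smaller shape means wider spread); a prior-year count that is Poisson at the same rate; exponential time to first event; patient-level HR 0.60 or 1. Two Cox models were compared: arm alone, and arm plus x = log(1 + count). Each setting used 3,000 trials of 60, plus one run of 40,000 patients for the limiting HR. The shift from a 0.5 SD imbalance is (coefficient of x) × 0.5 × SD(x).

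**4. Results at patient-level HR 0.60** (first figure arm alone, second with the count)

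| Mean/yr, shape | Events | Limiting HR | SE of log HR | Power % | Shift in log HR |
|---|---|---|---|---|---|
| 2, 0.7 | 15.9 | 0.674 / 0.627 | 0.518 / 0.536 | 10.1 / 12.8 | 0.438 |
| 2, 1 | 16.7 | 0.649 / 0.624 | 0.508 / 0.520 | 13.0 / 14.9 | 0.370 |
| 2, 2 | 17.9 | 0.623 / 0.613 | 0.493 / 0.498 | 14.8 / 16.0 | 0.233 |
| 3, 0.7 | 20.6 | 0.672 / 0.613 | 0.451 / 0.464 | 12.7 / 17.8 | 0.489 |
| 3, 1 | 22.0 | 0.665 / 0.624 | 0.439 / 0.449 | 14.4 / 20.2 | 0.410 |
| 3, 2 | 23.9 | 0.624 / 0.611 | 0.421 / 0.426 | 17.3 / 18.7 | 0.270 |

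- **Imbalance.** The shift is 0.23 to 0.49, which multiplies the HR by e^0.233 = 1.26 to e^0.489 = 1.63. Relative to the arm-alone SE this is 0.233/0.493 = 0.47 to 0.489/0.451 = 1.08. A separate simulation measured the arm-alone shift directly at about 0.20 to 0.47, with about 0.1 or less remaining after adjustment.
- **Attenuation.** ln 0.60 = −0.511. The arm-alone limits run from ln 0.623 = −0.473 (7% closer to 0) to ln 0.674 = −0.395 (23% closer).
- **Precision.** The SE rises in every row, by 1.0% (0.493 to 0.498) to 3.5% (0.518 to 0.536). Root mean squared error around log 0.60 does not fall in any setting either (for example 0.561 to 0.579, and 0.433 to 0.434).
- **Power.** The gain is 1.2 to 5.8 points.

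**5. At true HR 1.** Limiting HRs were 0.975 to 1.009 across both models, which also shows the simulation noise. Rejection was 3.5% to 5.2% with arm alone and 4.4% to 5.6% adjusted, so both are close to nominal. The imbalance shift was 0.24 to 0.49, so this exposure does not depend on a true effect.

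**The case against.** The strongest reply is that the point rests on silence. The Protocol does not say that arm is the only term, it uses the loose phrase of a similar manner, and it promises a full statistical analysis plan that could add a covariate. The Poisson model for critical errors names none either, which fits ordinary brevity. This stands in part: a reader might infer that an unadjusted analysis is prescribed, and the text does not go that far. But the model is specified by reference to one without a covariate, in a section that names the baseline value for its ANCOVAs and mixed model. An analysis plan that follows it would inherit the gap.

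Other strong readings are tempting and should not be adopted:

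- **That the hazard ratio is biased or invalid.** It is a valid marginal estimate with correct type I error. Attenuation is relative to the patient-level ratio and disappears at HR 1.
- **That adjustment buys precision or large power.** The interval for the log HR does not narrow. A gain from about 40% to 53% can be produced, but it needs an assumed HR of 0.40, 4 exacerbations a year and very wide spread. The Protocol says the sample size does not rest on testing a hypothesis. Every participant has also just exacerbated, so near-zero-rate patients are under-represented; allowing for that cut the gain in this extreme setting to about 6 points.
- **That the number of exacerbations is analysed without adjustment.** The outcome "The number of exacerbations by study completion 90(+/- 7) days" is listed, but no model for it is described, so nothing can be said about its covariates.
- **That the definitive trial's sample size would be wrong.** The Sample size rationale carries forward the variance of the chosen primary outcome, not this hazard ratio.

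**Conclusion.** The point holds as a minor, low-cost improvement. The Cox model for time to exacerbation names no covariate, while the obvious one is collected before an unstratified randomisation. The main reason to use it is protection when the arms are seen to differ: about 1 trial in 20 would have an imbalance of 0.5 SD or more, and 0.5 SD moves the log HR by about 0.2 to 0.5. Secondary is the modest attenuation, from a patient-level 0.60 to about 0.62–0.67 without the count, against 0.61–0.63 with it.

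The 5% follows from 30 per arm alone. The other sizes rest on assumed rates of 2 to 3 per year, the assumed spread, and a prior-year count that reflects the same underlying rate as follow-up. The benefit is conditional on the imbalance that occurs; averaged over all trials, the spread of the log HR does not fall. No stated sample size or precision figure changes.

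**What to change.** Add one sentence where Statistical Methods introduces time to exacerbation: the Cox model includes the prior-year exacerbation count from Visit 1, for example as log(1 + count), as a prespecified covariate beside arm, and the unadjusted hazard ratio is reported alongside. The sentence should also say whether the index exacerbation is included in the count, since it normally falls within that year.

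The cost is small. The variable is already collected, and the supplementary missingness table shows no missing Month 0 exacerbation counts among the 41 participants tabulated (it leaves out the six who withdrew). One degree of freedom is spent with few events, about 16 to 24 under the assumptions above at HR 0.60. The adjusted ratio is conditional on prior count and not marginal, so the two estimates answer slightly different questions and should be labelled as such.
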